### **5.2.3. Other Eligibility Criteria Considerations**

To assess any potential impact on subject eligibility with regard to safety, the investigator must refer to the following document(s) for detailed information regarding warnings, precautions, contraindications, adverse events, and other significant data pertaining to the GSK investigational product(s) or other study treatment being used in this study: SB705498 IB [GlaxoSmithKline Document Number [HM2004/00078/07](#)]

## **6. DATA ANALYSIS AND STATISTICAL CONSIDERATIONS**

### **6.1. Hypotheses and Treatment Comparisons**

#### **6.1.1. Part A**

##### **Precision Estimation**

Part A of the study is designed to estimate the dose response of SB705498 on the area of induced flare caused by capsaicin as measured by a laser Doppler imaging machine. No formal hypothesis will be tested.

#### **6.1.2. Part B**

Part B of the study is designed to test for superiority. The null hypothesis for the treatment comparison will be that there is no difference between the chosen dose strength of SB705498 and placebo on the average itch intensity post application of cowhage and histamine stimulant. The alternative hypothesis will be that there is a difference. Symbolically, this is expressed as follows:

$$H(0): \mu(\text{test}) = \mu(\text{reference})$$

$$H(1) : \mu(\text{test}) \neq \mu(\text{reference})$$

A two-sided t-test with  $\alpha=0.05$  will be used to test this hypothesis

### **6.2. Sample Size Considerations**

#### **6.2.1. Sample Size Assumptions**

##### **Part A**

Based on a within subject coefficient of variation of 0.45 which was observed as the variability estimate for SB705498/001 oral dosing, [GlaxoSmithKline Document Number [HM2005/00272/00](#)], for the reduction in area of flare as caused by capsaicin challenge and assessed by LDI machine, and a sample size of 16 subjects in a crossover design provides a precision estimate of 37.7%.

The precision estimates the half width of the 95% confidence interval around the difference between treatments. It is estimated that the lower and upper bounds of the 95% confidence intervals for the ratio of SB705498: placebo will be within point estimate  $\pm$  precision estimate. Hence, for the area of flare endpoint it is estimated that the 95% confidence interval will be within  $\pm 37.7\%$  if the within subject standard deviation is similar to that observed in SB705498/001 [GlaxoSmithKline Document Number [HM2005/00272/00](#)].

**Part B**

Part B of the study will be powered to detect a 20 point difference between the chosen dose of SB705498 and placebo on the 0-100 computerised VAS scale. An estimate of the variability of the computerised VAS scoring of itch after application of cowhage and histamine was obtained from an academic experiment performed by [name] et al. (Personal communication). The variability of itch on the 11 point (0-10) VAS scale for cowhage and histamine was 0.97 and 1.15 respectively. Using the higher value as our estimate of variability and with a clinically relevant difference of 2 points on the VAS scale then to have at least 90% power and with a two-sided type 1 error rate of 5%, 10 subjects are required for the crossover design.

**6.2.2. Sample Size Sensitivity****Part A**

The upper limit of the 95% confidence interval for the estimate of the coefficient of variation from the oral dosing study [GlaxoSmithKline Document Number [HM2005/00272/00](#)] is 0.77. Using this as the expected measure of variability then a sample size of 16 subjects in a crossover design provides a precision estimate of 66.2%.

**Part B**

Assuming the standard deviation is 20% higher than was previously seen in the data provided by [name] [[[name], 2000](#)], then under the same criteria as previously specified; clinically relevant difference of 2, 90% power and a 5% two-sided type 1 error rate, then 14 subjects would be required using this crossover design.

**6.2.3. Interim Analysis**

Data from Part A of the study may be analysed instream if the recruitment of subjects is slower than anticipated. The GSK study team will decide if this is necessary and when it should take place. Only the primary endpoint of Part A will be analysed at the interim analysis and will be analysed as per the final analysis for Part A as discussed in Section [6.2.4](#).

**6.2.4. Final Analyses****Part A**

An appropriate dose response model will be fit to the post dose time points. We are currently unsure as to what the underlying distribution of the dose response curve is so the data will be plotted to get a visual representation of the data. After this, various models will be applied and the best fitting one will be selected.

If the data does not allow for a dose response model to be fit then area of flare will be analysed using a mixed effects repeated measures model, fitting terms for treatment, period, time, and treatment time as fixed effects and subject as a random effect. No baseline will fit in the model since no area of flare is present until the stimulant is added. Point estimates and 95% percent confidence intervals for the difference between and placebo will be constructed using an appropriate variance structure.

Model and distributional assumptions underlying all analyses will be assessed by visual inspection of residual plots. Homogeneity of variance will be assessed by plotting the raw residuals against the predicted values from the model, whilst normality will be assessed using normal probability plots. Normality of the subject effect estimates from the random term will be assessed using a normal probability plot. Alternative statistical procedures will be considered should the model assumptions be violated.

## **Part B**

Average itch will be analysed using a mixed effects model, fitting terms for treatment, period and stimulant, as fixed effects and subject as a random effect. No baseline will fit in the model since no itch is present until the stimulant is added. Point estimates and 95% percent confidence intervals for the difference between and placebo will be constructed using the appropriate variance structure.

Model and distributional assumptions underlying all analyses will be assessed by visual inspection of residual plots. Homogeneity of variance will be assessed by plotting the raw residuals against the predicted values from the model, whilst normality will be assessed using normal probability plots. Normality of the subject effect estimates from the random term will be assessed using a normal probability plot. Alternative statistical procedures will be considered should the model assumptions be violated.

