One common disease with pruritus as a key symptom is atopic dermatitis (AD), which is frequently described as "the itch that rashes." Intensely itchy patches form. These patches can be widespread or limited to a few areas. Scratching often leads to redness, swelling, cracking, "weeping" of clear fluid, crusting, and scaling of the skin. TRPV1 has been shown to be upregulated in AD-skin lesions, and the activation of TRPV1 causes the release of proinflammatory and pruritic mediators ([Steinhoff, 2004](#); [Hutter, 2005](#); [Imamachi, 2009](#)). The activation of TRPV1 leads to the release of substance P and subsequently upregulates neurokinin-1 receptor ([Velazquez, 2002](#); [Hutter, 2005](#)). Substance P can contribute to the development of neurogenic inflammation and pruritus, and neurokinin-1 receptor antagonists can suppress scratching behaviours ([Ohmura, 2004](#); [Yamaoka, 2007](#) and [Kawana, 2007](#)), [Yun, 2011b](#)) have shown that a novel TRPV1 antagonist (PAC-14028) can suppress scratching behaviours in a mouse model of AD, through the inhibition of TRPV1 activation. This suggests that the antipruritic effect of TRPV1 antagonist in AD may be explained, at least in part, by the suppression of substance P release.

SB705498 is a potent and selective antagonist at the TRPV1 receptor and has previously been explored for inflammatory pain, migraine and allergic and non-allergic rhinitis. Topical administration of SB705498 provides a means to examine the role of this mechanism on pruritus and hence it's therapeutic potential.

This proposed experimental medicine study will consist of two sections. Part A has been designed to establish whether the formulation is capable of delivering SB705498 to the proposed site of action, and to select an appropriate dose for Part B. Part B will examine the effect of SB705498 on pruritus initiated by a histaminergic and a non-histaminergic pathway, using two different challenge agents. This may provide important information about the role of TRPV1 in pruritus and the therapeutic potential of SB705498.

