## **1.5. Rationale**

### **1.5.1. Study Rationale**

The aim of this study is to answer important questions about the role of transient receptor potential vanilloid type I (TRPV1) in pruritus. The study will use a topical formulation of SB705498, a selective TRPV1 antagonist.

In order to establish whether the topical formulation enables SB705498 to reach the site of action the TRPV1 agonist, a capsaicin challenge will be performed where capsaicin is applied to the volar forearm. Capsaicin is a highly selective and potent (low nanomolar affinity) exogenous agonist for the TRPV1 receptors present on polymodal mechano- and heat sensitive C fibres and mechano heat sensitive A $\delta$ -fibers. These nerve fibres transmit both pain and itch. Capsaicin application will produce a flare on the skin.

In Part A three different doses of SB705498 will be tested together with a placebo formulation. Evidence that the SB705498 is reaching the site of action will be ascertained by a difference in the capsaicin induced flare on the SB705498 dosed area compared to the flare produced by the capsaicin on the placebo controlled area.

The dose of SB705498 producing the largest and/or most consistent average reduction in flare will be selected for Part B of the study. If no effect is observed in Part A then Part B will not be conducted.

In Part B of the study the effects of SB705498 on two pruritogens (cowhage and histamine) which produce itch induction by two different mechanisms will be assessed.

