#### **1.5.4. Histamine**

Histamine has been used for many decades as the experimental pruritogen of choice in numerous studies. [Melton, 1950; Ishiuj, 2009] In chronic pruritic disease the histaminergic pathway does not appear to be the most relevant pathway. However potent histamine H1 and H2 antagonists such as Doxepin have been shown to reduce pruritus significantly in a number of pruritic diseases such as AD, lichen simplex chronicus, contact dermatitis and nummular dermatitis, so histamine does play a role [Drake, 1994, Drake, 1995].

An understanding of the impact of SB705498 on pruritus initiated by cowhage or histamine may support the exploration at later stages of pruritic indications.

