| Administration of SB705498
cream/Placebo  |                                                                |                               | X  |    |       |             | X  |    |       |                                                |
| Histamine challenge                          | X                                                  |                               |    |    |       |             |    | X  |       |                                                |
| Cowhage challenge                            | X                                                  |                               |    | X  |       |             |    |    |       |                                                |
| COVAS scale                                  |                                                                |                               |    | X  | X     |             |    | X  | X     |                                                |
| Adverse Event Review                                     | X                                                              | ←=====→                       |    |    |       |             |    |    |       | X                                              |
| Concomitant Medication Review                            |                                                                | ←=====→                       |    |    |       |             |    |    |       | X                                              |

1. COVAS will be measured continuously from 1-2 mins before application of challenge agent and for a maximum time of 15 mins post application.
2. Screening assessments for Part B will only occur if the period of time between Part A screening and Part B study visit 1 exceeds 60 days.
3. To be performed for new subjects that have not taken Part in Part A.
4. Application of the cream/placebo followed by challenge agent assessment will be performed twice on each day. i.e. 4 applications over the 2 days with both SB705498 and placebo and each challenge agent.
5. The days on which the cowhage and histamine challenges are performed may be swapped according to site logistics and at the investigators discretion.

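### The Part B primary model has no treatment-by-stimulant term, so it gives one drug effect averaged over cowhage and histamine and cannot show which itch pathway responds; adding the term is a cheap improvement.

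*Protocol*

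**What the plan says.** Section 6.2.4 (Part B) fixes the primary model by "fitting terms for treatment, period and stimulant, as fixed effects and subject as a random effect", and promises a point estimate and 95% CI for the difference from placebo. No interaction term, separate model per stimulant or stimulant-specific contrast appears anywhere in the protocol.

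The purpose is put in terms of two pathways:

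- Section 1.1: "Part B will examine the effect of SB705498 on pruritus initiated by a histaminergic and a non-histaminergic pathway, using two different challenge agents".
- Section 1.5.1: "two pruritogens (cowhage and histamine) which produce itch induction by two different mechanisms will be assessed".
- Section 1.5.4: "An understanding of the impact of SB705498 on pruritus initiated by cowhage or histamine may support the exploration at later stages of pruritic indications".

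Section 4.2 (Part B) uses sequences that compare active with placebo on opposite forearms within each challenge. Section 6.1.2 states one null hypothesis that names both stimulants, and the objective in Section 2.2.1 also names both without saying pooled or separate.

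The sample size in Section 6.2.1 rests on stimulant-specific SDs of 0.97 (cowhage) and 1.15 (histamine) on the 0-10 scale: "Using the higher value as our estimate of variability and with a clinically relevant difference of 2 points on the VAS scale". It arrives at 10 subjects. For comparison, the fallback model for Part A is written as "fitting terms for treatment, period, time, and treatment time as fixed effects", which is most naturally read as including treatment-by-time. The protocol therefore names a combined term there but not in Part B.

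**The concern.** A model with treatment and stimulant as main effects assumes that the drug effect is the same for both agents. The protocol's own rationale gives reason to doubt this: Section 1.5.3 says that cowhage acts on nerve fibres distinct from those activated by histamine.

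If only one pathway responds, the primary result is a diluted effect on itch in general. If the effects run in opposite directions, they cancel. In neither case does the primary result say which agent responded, although that is what Section 1.5.4 wants to carry into later indications. If per-stimulant contrasts are chosen only after the data are seen, they are post hoc.

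**Working it through.** **Inputs.** Difference 2 points on the 0-10 scale, which is 20 on the 0-100 COVAS; SD 1.15, which is 11.5 on COVAS; two-sided 5%; at least 90% power; 10 subjects (all Section 6.2.1). Each subject has four applications, active and placebo within each stimulant (Section 4.2). Assumptions: 11.5 is the within-subject SD, equal for both stimulants, and carries over to the 15-minute average. All powers use the noncentral t.

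**1. The plan's own figure.** For one stimulant, SE = 11.5 × √(2/n) with n - 2 df.

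- n = 9: power 88.4%.
- n = 10: SE = 11.5 × √(2/10) = 5.14, 8 df, power 92.4%.

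So 10 is the smallest n that reaches 90%, and the stated figure reproduces as a single-stimulant crossover.

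**2. What the written model estimates.** Each subject contributes two active-placebo pairs, so SE = 11.5 × √(2/20) = 3.64. The treatment coefficient is the mean of the two stimulant effects. For a common effect of 20 points its power is 99.95%.

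**3. Unequal effects under the written model.** Take true effects of 20 (cowhage) and 0 (histamine).

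- Pooled estimate: (20 + 0)/2 = 10.
- With the SD left at 11.5, the formula gives 75% power. This is too high, because the additive model does not fit. The best additive fit misses each of the four cell means by 5 points, so the residual sum of squares gains 40 × 5² = 1000.
- With all subjects in the tabled order (cowhage first) there are 26 residual df. The residual variance rises from 11.5² = 132.25 to about 132.25 + 1000/26 = 170.7 (SD 13.1), and the SE as estimated is about 4.1.
- Simulation of the 10-subject design gives significance in about 66% of trials. The same holds for most ways of mixing the stimulant order; one allocation that ties order to sequence gave about 71%.

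| True effects | Pooled estimate | Significant |
|---|---|---|
| 20 and 20 | 20 | >99.9% |
| 20 and 0 | 10 | about 66% |
| 30 and 0 | 15 | about 92% |
| 20 and -20 | about 0 | about 0.5% |

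(The last row reached 1.5% in the same tied allocation.)

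**4. With treatment-by-stimulant added.** Each contrast has SE 5.14. The 95% CI half-width is 10.6 points (24 df) or 11.9 (separate crossover analysis, 8 df).

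- Power for 20 points at 0.05: 96% (24 df) or 92.4% (8 df).
- At 0.025 each: 92.5% (24 df) or 84.4% (8 df).
- With the SD 20% higher (13.8, the scenario in Section 6.2.2), at 0.05: 87% (24 df) or 81% (8 df).
- For true effects of 20 and 0, simulation returns 20 (96% significant) for the responding agent and 0 (about 5% significant) for the other.
- The interaction test itself has SE = 11.5 × √(4/10) = 7.27 and about 75% power for a 20-point difference between agents. It should not be the gate for reporting the two contrasts.

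**5. Multiplicity.** If either contrast counts as success at 0.05 each, the family-wise error is up to 1 - 0.95² = 9.75% (independent tests). If both must succeed, no adjustment is needed, but joint power is about 0.924² = 85% (8 df, independence).

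**6. Stimulant order.** With a four-level period and every subject in the tabled order, the design matrix has rank 14 for 15 columns, because stimulant is aliased with day. The treatment contrast is still estimable, with the same SE of 3.64. With period coded as first or second application within the day, the matrix has full rank (13 of 13).

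**The case against.** The strongest defence is that the model answers the hypothesis as written. Section 6.1.2 sets one null over both stimulants, Section 2.2.1 names both agents in one objective, and a pooled main effect is a valid test of that. The analysis plan is not shown and may add estimates by stimulant. This much stands: the conflict is with the aim, the rationale and the paired layout rather than with the hypothesis. But the protocol itself specifies the primary model terms, and the planned residual checks would not supply the missing contrasts.

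A reader might infer more, and the documents do not support it:

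- That the trial cannot answer its question. It can: active and placebo are paired within each challenge, so the planned data suffice. The limit is in the written model.
- That the inactive pathway would be declared significant. The model tests neither pathway. With effects of 20 and 0 the average is truly non-zero and rejection is correct; the risk lies in how the result is read.
- That the sample size is wrong. Section 6.2.1 never says that its calculation is per stimulant. If it is, 10 subjects over-power the pooled test and already support separate contrasts.
- That investigator discretion over challenge days ("The days on which the cowhage and histamine challenges are performed may be swapped according to site logistics and at the investigators discretion") invalidates the analysis. The aliasing in the tabled order affects only the separate stimulant and period effects, so it does not by itself require changing that footnote.
- That subject as the only random effect seriously distorts the SE. Any inflation depends on a subject-by-stimulant variance that the protocol does not give, would cost power rather than type I error, and Section 6.2.4 leaves the variance structure open.

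**Conclusion.** The point holds as a cheap improvement to the analysis wording, not as a fatal flaw. The written primary model returns one averaged effect: 10 points when the truth is 20 and 0, significant in about 66% of trials with nothing to show that one agent did not respond, and about 0 when the truth is 20 and -20. The sample size already supports a separate contrast for each agent at unadjusted 0.05 (92% to 96% power). Whether 90% is kept under a split alpha depends on the analysis: 84% with 8 df, 92.5% with 24 df. All figures assume that 11.5 is the within-subject SD and applies to both agents.

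**What to change.** In Section 6.2.4 (Part B), add treatment-by-stimulant as a fixed effect. Report the active-placebo difference with a 95% CI for cowhage and for histamine, beside the pooled contrast. Do not make these contrasts conditional on a significant interaction.

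State before unblinding whether success means either agent or both. If either, control the family-wise error, for example by Holm or 0.025 each. If both, test each at 0.05 and accept the lower joint power. Align the hypothesis in Section 6.1.2 with the choice.

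A subject-by-stimulant random effect is a reasonable optional refinement. No change to the stimulant-order footnote is needed for this point.

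The cost is a few lines of wording and the multiplicity shown above. No extra subjects, visits or data are needed at the stated SD if each contrast is tested at 0.05.

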### **6.2.4.1. Safety Analyses**

Safety data will be presented in tabular and/or graphical format and summarized descriptively according to GSK's Integrated Data Standards Library (IDSL) standards.

### **6.2.4.2. Pharmacokinetic Analyses**

If sufficient PK data is quantifiable then appropriate analyses of the pharmacokinetic parameters, will be performed and will be documented in the RAP.

### **6.2.4.3. Pharmacokinetic/Pharmacodynamic Analyses**

The relationship between time, concentration and the pharmacodynamic responses (as outlined in primary and secondary objectives) following topical administration of SB705498/ placebo and will be explored by graphical means where appropriate.

Further analysis using non-linear mixed effect models may be performed by CPMS if deemed appropriate

## **7. STUDY ASSESSMENTS AND PROCEDURES**

This section lists the parameters of each planned study assessment. The exact timing of each assessment is listed in the Time and Events Table (Section 4.4). Detailed procedures for obtaining each assessment are provided in the Study Procedures Manual (SPM). Whenever vital signs, 12-lead ECGs and blood draws are scheduled for the same nominal time, the assessments should occur in the following order: 12-lead ECG, vital signs, blood draws. The timing of the assessments should allow the blood draw to occur at the exact nominal time.

The timing and number of planned study assessments, including safety, pharmacokinetic and pharmacodynamic assessments may be altered during the course of the study based on newly available data (e.g. to obtain data closer to the time of peak plasma concentrations) to ensure appropriate monitoring. The change in timing or addition of time points for any planned study assessments must be approved and documented by GSK, but this will not constitute a protocol amendment. The IRB/IEC will be informed of any safety issues that require alteration of the safety monitoring scheme. No more than 500 mL of blood will be collected over the duration of the study, including any extra assessments that may be required.

